## Abstract

**Background:** Refugee populations are at substantial risk of developing substance use disorder (SUD) and other mental health disorders. At the same time, refugee populations face numerous barriers to accessing mental health services. Digital interventions can address some of these issues, as emerging evidence indicates that digital interventions offer an effective, low-cost alternative with high accessibility and similar efficacy as standard SUD prevention programs. As an add-on to traditional services, they further present a viable approach to the lack of personnel available for foreign language communication in preventive and therapeutic settings. In the present study, we thus aim to develop and evaluate a digital health intervention (DHI) for the reduction of substance use for young refugees with problematic use of alcohol and/or cannabis. The intervention will be implemented in a smartphone app, translated into Arabic, English, Farsi, German, and Pashto, and is to be used stand-alone. It is based on methods from cognitive behavioral therapy, contains culturally adapted elements, provides practical information on how to deal safely with alcohol and cannabis, and motivates behavior change through increased self-reflection and behavioral, cognitive, and emotional skills-training in interactive exercises.

**Methods:** We conduct a single-armed feasibility trial among 150 young refugees with problematic use of alcohol and/or cannabis. Participants will receive a digital screening and digital health intervention (DHI) for the reduction of problematic substance use, carried out over a 4-week time frame. The primary outcomes are the intervention's feasibility and the target population's acceptance of the intervention. The secondary outcome is a change in substance use post-intervention from baseline. Measurements are taken pre-intervention (baseline), post-intervention (after 4 weeks), and at 3- and 6-month follow-ups. We expect the intervention to be feasible and accepted by the target group.

**Discussion:** The present study will establish to what degree the digital intervention (the “BePrepared App”) is feasible and accepted by the target group. The evaluation of an easily accessible, feasible, and accepted intervention may impact refugees' mental health and health-related consequences. It aims at overcoming barriers to preventive health care in the substance use field for underserved refugee populations as a tool within a larger set of urgently needed interventions.

**Trial Registration:** DRKS00021095 at the “German Clinical Trials Register” (30.03.2020).

## Background

In the end of 2019, the United Nations High Commissioner for Refugees (UNHCR) estimated a number of 79.5 million forcibly displaced people, i.e., people who are driven from their homes by persecution, conflict, violence, human rights violations, or events seriously disturbing public order. This is a record high, which accelerated in recent years as a response to the armed conflicts in Syria, but also conflicts in other areas like the Middle East, parts of sub-Saharan Africa, and the persecution of the Rohingya people in Myanmar (1). In 2019, the largest single group of people asking for asylum in Germany were of Syrian origin (27.3%, *n* = 39.270), followed by people of Iraqi origin (9.5%, *n* = 13.742) ranked second, Turkish origin (7.4%, *n* = 10.784) ranked third, Afghan origin (6.7%, *n* = 9.522) ranked fourth, Nigerian origin (6.2%, *n* = 9.070) ranked fifth, and Iranian origin (5.7%, *n* = 8.407) ranked sixth (2). On the basis of the 1951 Refugee Convention, a refugee is protected by international law and defined as “someone who is unable or unwilling to return to their country of origin owing to a well-founded fear of being persecuted for reasons of race, religion, nationality, membership of a particular social group, or political opinion” [(3), p. 3]. On their website, the UNHCR further describes refugees as “people who have fled war, violence, persecution and have crossed an international border to find safety in another country” [(4), para. 1]. For ease of reading, we will use the word *refugee* interchangeably with the terms *forcibly displaced people* and *forced migrants*.

There is an urgent need to support the mental health of refugees (5), who are in a particularly vulnerable situation due to exposure to trauma and other adverse health effects before migrating from their homes in conflict-affected settings, during their journey, and upon arrival in intermediate and final receiving countries (6, 7). Though estimates regarding refugees' mental health vary widely, a growing number of studies and meta-analyses suggest an elevated risk for mental health disorders in refugees [for an overview see Henkelmann et al. (8), Silove et al. (9), and Crepet et al. (10)]. New WHO estimates adjust previous estimates upwards, showing a high prevalence of mental health disorders among people affected by conflict and war. Of these, one person in five (22.1%) lives with some form of depression, anxiety disorder, post-traumatic stress disorder (PTSD), bipolar disorder, or schizophrenia, compared to the general population in which “only” one person in 14 with any mental disorder worldwide does (11). The Federal Chamber of Psychotherapists in Germany (12) estimated in 2015 that 40–50% of refugees in Germany suffer from PTSD or depression. Of the (mostly West African) refugees who arrived in Italy in 2015, ~89% experienced possibly traumatic events during their often partly seaborne migration (10). Less data on experienced trauma is available for refugees arriving to Greece crossing the Mediterranean Sea, the majority of refugees having fled Syria (57%), Afghanistan (22%), and Iraq (5%) (until mid 2015) and most of which wanting to settle in Germany or Sweden (13).

In the general population, evidence from longitudinal (14–16) and experimental studies (17, 18) suggests that certain mental health disorders, such as PTSD, previous alcohol or drug use, depressive or anxiety disorders, predict later alcohol abuse or dependence and illicit drug abuse and dependence. The Diagnostic and Statistical Manual of Mental Disorders, Fifth Edition (DSM-5), merges *substance abuse* and *substance dependence* into a single classification of *substance use disorder* (SUD). On a continuum from mild to severe, it describes “a cluster of cognitive, behavioral, and physiological symptoms indicating that the individual continues using the substance despite significant substance-related problems” [(19), p. 483]. *Problematic, harmful, or hazardous substance use* describes an absence of a current substance-related disorder, however, increases the risk of harmful consequences, including physical, mental, and social problems for the user or others (20). It predicts the development of substance use related harm such as SUD, social problems, and the utilization of health care services (21).

According to the United Nations Office on Drug and Crime World Drug Report (22), risk factors for substance use are a refugee status, poverty, conflict/war, homelessness, social exclusion and inequality, neighborhood disorders, peer substance use and drug availability, mental health problems, trauma and childhood adversity. Problematic use of substances and the transition to SUD are known to have a higher prevalence in people with a lower socioeconomic status [SES; e.g., Legleye et al. (23)] as well as in people with certain mental disorders (14–18).

Initial research suggests that displacement experiences, their potential consequences and conditions in hosting countries (e.g., uncertain future prospects) may increase vulnerability to substance use, its impact and the transition to more harmful patterns of substance use (24). From an epidemiological viewpoint, substance use and its harmful consequences are common among refugee populations. For example, systematic reviews identify prevalences of problematic alcohol use between 17 and 36% in camp settings and 4–7% in community settings (25) and high levels of opioid use due to forced displacement that is caused by armed conflict in Pakistani and Afghan populations (26). Initial research on the drug use and special needs of refugees in Germany shows that 28.4% of a sample of predominantly Iranian and Afghan refugees interviewed in low-threshold addiction services have started using alcohol and/or illicit drugs *after* leaving their home country. 16.4% of the interviewed people were occasionally consuming alcohol and cannabis, the most-used substance being opioids (27). According to qualitative research based on expert interviews, substance-using unaccompanied minor refugees are primarily using alcohol or cannabis and have started using after arrival in Germany (28). Although remaining under the national average, data from the transcultural psychiatric department in Vienna, Austria, shows an elevated alcohol consumption from patients with muslim background from the middle east, compared to the average consumption in their countries of origin (29). The opposite was shown for cannabis, where the reported consumption remained under the expected value, based on the comsumption pattern in the countries of origin. German law prohibits cannabis acquisition and possession while alcohol remains legal for adults. Increased alcohol consumption and decreased cannabis consumption among refugees might be heavily influenced by legal regulations and social norms in the country of stay. Generally, it was found that regardless of former protective factors such as religious background, consumption patterns adapt to the social majority ones when length of stay increases [e.g., Arfken et al. (30); Harris et al. (31)]. It still remains questionable to what extend protective effects of cultural and social norms can be attributed to the subgroup of forced migrants (25). Next to research on protective factors, further research is required to assess key risk factors, patterns of use, and the extent of conflict-associated harmful use of e.g., alcohol beyond a merely suggestive causal relationship (32, 33).

These results, including the high number of Iranian and Afghan refugees who have started using alcohol and illegal substances after leaving their home country or upon arrival in Germany and, furthermore, the elevated risk for a transition to more harmful patterns of substance use, highlight the need for low-threshold early and indicated prevention targeting (young) refugees; Especially since asylum seekers in Germany tend to become younger over the last 5 years, with a growing majority being underage and a second largest group being between 18 and 25 years old (34). Indicated prevention describes interventions in individuals who show a manifest risky or problematic behavior (35), such as problematic/hazardous substance use in the absence of SUD.

Despite a high risk for the development of mental health disorders, refugees have legal access to just very restricted areas of general health care in Germany (36) and, regarding mental health care in receiving countries, face numerous structural and socio-cultural barriers that limit accessibility and utilization of services (37).

Digital health interventions (DHI) can address some of these barriers and can thus have an impact on the delivery of addiction prevention or harm reduction to marginalized populations. Structurally, DHI have the potential to reduce barriers such as a lack of resources, language barriers, and bureaucracy. As an example, Calvo et al. (38) demonstrated the accessibility of a smartphone app aimed at reducing harm associated with intravenous drug consumption among homeless drug users. Socio-culturally, DHI work with a high level of privacy and can reduce fear of stigma and discrimination (39), which would otherwise represent major barriers for individuals with substance use problems to seeking treatment (40). Furthermore, they may lower the impact of shame on utilization of services and bypass the necessity to ask for help personally; all of which were commonly seen as barriers to accessing traditional mental health care in Syrian refugees (37).

The majority of Syrian and Iraqi refugees in Germany have had access to a smartphone during migration (78 and 87%, respectively), do so upon arrival in Germany (89 and 92%, respectively), and use the internet daily (86 and 82%, respectively) (41). Therefore, we assume a high accessibility of smartphone-based DHI, e.g., apps, for the present study's target group. This, however, under two assumptions: first, that Afghan, Iranian, Iraqi, and Syrian refugees in Germany show a similar behavior toward apps and their usage in terms of needs and concerns as the German population. Second, that after cultural adaptations, content meets these needs also in terms of values, worldview, and cultural customs of the targeted population (42, 43). Otherwise, new barriers to accessing digital health care may arise (e.g., lack of technical literacy, difficulties accessing the internet, a doubt in the credibility, or low acceptance of services) (44). In terms of effectiveness, DHI have shown to be effective in reducing problematic use of alcohol compared to either no intervention or merely providing general health information and show similar effects as face-to-face interventions (45). The clinical significance for stand-alone and thus purely self-guided DHI is less clear compared to blended and therapist-guided digital approaches (46). As a strength—however—they may present a viable approach to the lack of language skills and cultural competencies of clinicians, but most importantly to lacking legal access to mental health care and unclear cost coverage for refugees in intermediate or final receiving countries, e.g., Germany. This leaves evidence-based stand-alone DHI a scalable and low-threshold service in reaching marginalized populations, such as refugees, who would face difficulties to make use of mental health services otherwise.

### Objectives

This study protocol describes the development and evaluation of a digital health intervention (DHI) for indicated prevention of SUD in young refugees in terms of its acceptance and usability in a single-armed feasibility trial. Additionally, the initial efficacy in reducing problematic use of alcohol and/or cannabis will be assessed by comparing pre- and post-intervention prevalence measures. As intervention, all participants will have access to the BePrepared App, which is an evidence-based stand-alone DHI optimally to be used in the participant's mother tongue and therefore available in Arabic, English, German, Farsi, and Pashto.

## Methods

We (1) developed and (2) plan to evaluate a digital health intervention (DHI) for the reduction of problematic substance use for young refugees from Afghanistan, Iran, Iraq, and Syria, aged 18 to 28 years. The targeted group shows signs of problematic use of alcohol and/or cannabis (see *Assessments* for details on the assessment of problematic substance use during the screening) and currently lives in Germany. This study protocol describes both steps (i.e., development and evaluation) following the recommendations of the SPIRIT 2013 statement [Standard Protocol Items: Recommendations for Interventional Trials; (47)].

### Development of the Digital Health Intervention

#### Theoretical and Clinical Framework

The digital health intervention's aim is the reduction of problematic substance use. The intervention is technically implemented in form of a smartphone application for stand-alone use. Overall, we aimed to develop a smartphone application that is easily understandable, rewarding (including positive reinforcement and feedback about progress), and beneficial [such as proposed by Crane et al. (48) for apps aiming at reducing excessive alcohol use]. The intervention development is further based on the IDEAS (Integrate, Design, Assess, and Share) framework for developing digital health behavior change interventions by Mummah et al. (49) as it may apply to the development of a digital behavior change intervention and its evaluation in a feasibility trial. The IDEAS framework consists of 10 phases: (1) empathize with target users, (2) specify behavior, (3) ground in behavioral theory, (4) ideate implementation strategies, (5) prototype potential products, (6) gather user feedback, (7) build minimum viable product, (8) pilot potential efficacy and usability, (9) evaluate efficacy in RCT, (10) share intervention and findings. In line with phase 1 and 6 of IDEAS, we took the following steps to ensure user-involvement with the hard-to-reach target group and to uncover needs, desires, and motivations of the target users:

Conduction of two focus groups [one with refugees of the targeted countries of origin (*n* = 7) and one with experts from the field of refugee and addiction services (*n* = 13)],Consultation with professional cultural mediators (*n* = 5),Consultation with the advisory board of refugees of the “PREPARE research consortium on the Prevention and Treatment of Substance Use Disorders in Refugees,”Pilot-testing including interviews with young refugees (*n* = 9) gathering user feedback.

The conceptual design of the intervention (phase 3) is based on principles of cognitive behavioral therapy and implements selected behavior change techniques [following Michie et al. (50) taxonomy, see Table 1]. In an interdisciplinary team of psychologists, computer scientists, and app designers, the conceptual design, technical implementation, and app development took place in an iterative approach (phases 4, 5, and 7). Due to the study design, phases 2, 9, and 10 were skipped. For details on phase 8, please see *Evaluation of the digital intervention*.

**Table 1 T1:** Content of the digital intervention.

**Module**	**Purpose**	**Exercises**	**Behavior change techniques incorporated [2]**
**Personalized feedback [1]** (see Figure 1)	• Informing about the user's substance use • Promote responsibility and self-efficacy • Referral to addiction treatment facilities in case of indications for alcohol or cannabis use dependence		• Provide information on social norms • Personalized normative feedback (comparison to people of same age and gender in the German population) • Motivational Interviewing techniques
**Diary** (main module 1, see Figures 2C, 3)	• Enhancing self-monitoring • Encouraging to reflect on substance use and situations in which one uses • Giving insight in the amount of pure alcohol (g) of different beverages	• Substance use diary	• Prompt self-monitoring of behavior • Foster identification of cues
**Goals** (main module 1)	• Introducing realistic goal setting	• Personalized goal-setting	• Prompt specific goal setting • Prompt review of behavioral goals • Provide feedback on behavior based on principles of Motivational Interviewing
**Changing** (main module 2, see Figure 4)	• Breaking down behavioral choices into the underlying motives • Reflecting on values	• Motivational “Scale” • “Values”	• Pros and cons of consumptions vs. non-consumption • Identification of incompatibility between beliefs and behavior • Prompt barrier identification • Feedback on motives based on principles of Motivational Interviewing • Prompt intention formation
**Thinking and Doing** (main module 3)	• Practicing to reject substance use • Activity planning • Activation of resources	• “No, thank you” • “Positive thoughts” • “Planning activities”	• Skills training with focus on thoughts and behavior • Rejection training • Prompt self-talk • Behavioral activation
**Relaxation** (main module 4, see Figure 5)	• Informing about emotions and their purpose • Learning how to regulate emotions • Calming down body and mind by breathing	• How to deal with sadness, anger, fear and nightmares • Breathing exercise	• Skills training with focus on emotions and behavior • Psychoeducation on emotions and its purpose • Monitoring of emotional effects • Feedback on outcomes of breathing exercise
**Knowledge** (optional module)	• Enhancing knowledge on alcohol and cannabis, its use, its consequences, the German culture, the German legal system	• “Good to know” • Quiz	• Provide information about behavior-health link • Provide information about health, social and emotional consequences • Provide instruction on safer use • Provide information on social support (practical) • Foster identification of self as a role model
**Treasure chest** (optional module, see Figure 6B)	• Encouragement to use the diary • Encouragement to reach goals • Providing an overview of successes, feedback and highlights	• “Successes” (Badges) • Feedback • “Moments” • Incentives	• Activation of resources • Provide contingent rewards • Provide general encouragement
**Help** (optional module, see Figure 6A)	• informing about the care system • Creating contact to help offers online or in person		• Provide information on social support (practical)
**Why?** (optional module, see Figure 6C)	• Transparency: Informing about the purpose of the exercises • Weaken doubts • Enhancing motivation		• Provide information about behavior-health link • Provide information on consequences of the exercises • Provide instruction on the exercises

*1: following Kamya's (51) FRAMES model; 2: taxonomy following (52)*.

#### Structure and Content of the Digital Intervention

After baseline assessment, the intervention starts with all study participants receiving a digital personalized feedback (see Figure 1) on their substance use following a subjective normative approach (53) and the FRAMES (Feedback, Responsibility, Advice, Menu Options, Empathy, and Self-Efficacy) model by Kamya (51). Four main modules are unlocked every week in four consecutive weeks (see Figure 2A for a visualization of newly activated modules). These main modules include: (1) promoting self-monitoring via a substance use diary (see Figure 2C) and feedback in accordance with previously made entries (see Figure 3); (2) promoting motivation to change (see Figure 4); (3) promoting skills focusing on behavior and thoughts, and (4) promoting skills focusing on emotions including a breathing exercise (see Figure 5). Three further modules encompass psychoeducation (i.a. on safe handling of alcohol and cannabis, advice on substance use reduction, and legal regulations), activation of personal resources, and information on the addiction help system in Germany. These modules can be used optionally. During the 4-week intervention phase, participants can use the activated app content according to their own needs. Pending follow-up measurements will block further use of the app (see *Assessments*). For an overview of the modules, see Table 1.

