##### Referral Pathways

Participants with high scores on the AUDIT or the CUDIT-R that indicate an alcohol or cannabis use dependency, respectively, will receive personalized feedback that suggests and encourages to seek help, provides an example for a counseling center and, in the case of high alcohol use, the warning to “not stop consumption without professional help as it could lead to physical harm or danger (e.g., cramping).” Furthermore, the intervention provides information on addiction counseling centers in general and highlights reasons to seek support based on the criteria of ICD-10 (54). In a separate module (see Table 1; Figure 6A) a number to call a hotline for immediate assistance in crisis situations, selected counseling centers and a link to a further (German-wide) search list for addiction counseling centers, as well as additional relevant online applications, are provided.

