**Figure 7 F7:**
[figure not shown]
Implementation of the follow-measurements in the app. **(A)** Entry screen. **(B)** Examplary item of the overall assessment on the app. **(C)** Example item on cultural sensitivity.

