#### Participants

Study participants will be Afghan, Iranian, Iraqi, and Syrian refugees living in Germany. We will recruit participants with a multi-strategic approach in Germany (see *Recruitment*).

During the onboarding of the app, written informed consent will be obtained. A screening in form of an online questionnaire will determine up to *n* = 150 refugees for eligibility for study participation.

Inclusion criteria are:

age between 18 and 28 years;country of origin being Afghanistan, Iran, Iraq, or Syria;self-declared refugee background;hazardous/problematic use of alcohol and/or cannabis determined as described below;informed consent to participate in the study;agreement with the application's terms of use.

Participants identified as eligible after study participation screening will be assigned to Group 1 (study participants). Participants that violate inclusion criteria (1) to (4), but are older than 18 years of age, to still be able to download and use the app and to be assigned to Group 2 (app users). This is in order to foster the dissemination of the app and to prevent systematic discrimination and potentially negative attitudes toward the app usage due to perceived unfairness. Minors are neither eligible for study participation nor app use.

Exclusion criteria for study participation are an age of under 18 years, a country of origin other than Afghanistan, Iran, Iraq, or Syria, no self-declared refugee background, no hazardous/problematic alcohol- and/or cannabis-use or negated consent to the study participation or the app's terms of use, and a current participation in an in- or out-patient treatment for SUD. For promoting dissemination, an exception is the participation in a group intervention program on substance use disorder and trauma (contact [name] at [contact] for more information) which will be assessed during the screening and which takes place within the “PREPARE research consortium on the Prevention and Treatment of Substance Use Disorders in Refugees”.

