#### Assessments

After obtaining informed consent and an eligibility screen on the app usage (minimum of 18 years of age), the baseline-measurement (t_0_) is scheduled. The baseline questionnaires will consist of items relating to sociodemographics, escape related information, a medical questionnaire on pregnancy, serious disease, medication and SUD, depression, anxiety, and smartphone use (see Table 2). Follow-up measurements are scheduled directly after the intervention (t_1_), as well as at 3-months (t_2_), and at 6-months (t_3_) follow-ups. Assessment and intervention take place on the participants' mobile devices and pending assessments will block further use of the app. A schedule of enrollment, intervention and assessment is shown in Figure 8.

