**Figure 8 F8:**
[figure not shown]
Schedule of enrollment, interventions and assessment. Completed SPIRIT 2013 figure of recommended content of enrollment, interventions, and assessments. t_0_, baseline; t_1_, 4 weeks after baseline (post intervention); t_2_, 16 weeks after baseline; t_3_, 24 weeks after baseline.

To assess problematic use of alcohol and/or cannabis, all participants receive a screening using the Alcohol Use Disorder Test [AUDIT; (63)] and a from 6- to 12-months adapted version of the Cannabis Use Disorder Test-Revised [CUDIT-R; (64)] at baseline t_0_. The AUDIT is a 10-item screening tool that assesses individual alcohol consumption, with scores for each question ranging from 0 to 4 (e.g., *never* scoring 0, e.g., *less than monthly* scoring 1, e.g., *monthly* scoring 2, e.g., *weekly* scoring 3, and e.g., *daily or almost daily* scoring 4) and overall scores ranging from 0 to 40. Scores of 0 to 5 and 0 to 4 indicate a safe use for males and females, respectively, scores from 5 to 19 and 4 to 19 indicate problematic use for males and females, respectively, and scores of 20 or higher is likely to indicate alcohol dependence. The CUDIT-R consists of eight items, screens individual cannabis consumption, with scores ranging from 0 to 4 (e.g., *never* scoring 0, e.g., *less than monthly* scoring 1, e.g., *monthly* scoring 2, e.g., *weekly* scoring 3, and *daily or alm*ost daily scoring 4). For all genders, a score of ≥ 8 and <12 represents problematic use of cannabis. The Generalized Anxiety Disorders Scale-7 [GAD-7; (65)] assesses symptoms of anxiety and consists of seven items, each scored from 0, *not at a*ll, to 3, *nearly every day*. Despressive symptoms are assessed with the Patient Health Questionnaire [PHQ-9; (57)], a screening tool that consists of nine items, as well as the GAD-7 items each scoring from 0, *not at all*, to 3, *nearly every day*. For the sources of translations see Table 2.

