##### Study Adherence

In order to lower the risk for dropout, participants will be informed on the study procedure including the time needed to complete the digital health intervention and the follow-up measurements, and on incentives. Group 1 will receive a €15 gift card as a reward for their participation after completing measurement t_1_, t_2_, and t_3_. Group 2 will participate in a tombola with a minimum one in ten chance of winning a €15 gift after completing the measurements at t_1_, t_2_, and t_3_.

There are regular reminders in form of push notifications with the goal to draw attention to unused intervention components, missed diary entries, and the follow-up measurements (see Figure 2B). Study adherence will be assessed through the app's meta-data log-files which give information on the frequency and duration of intervention use.

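### As worded, the assessment lock covers the whole app, so a pending t1, t2 or t3 questionnaire stands in front of the Help module and its crisis hotline until it is completed

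*Protocol article*

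**What the plan says.** The lock is stated twice. Structure and Content of the Digital Intervention says "Pending follow-up measurements will block further use of the app" and refers the reader to Assessments. That section says "pending assessments will block further use of the app". Both sentences are about the app as a whole.

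Referral Pathways describes a separate module containing "a number to call a hotline for immediate assistance in crisis situations", selected counseling centers, a link to a Germany-wide search list and further online services. Table 1 identifies it as Help, one of the optional modules, with the stated purpose "Creating contact to help offers online or in person". The legend to Figure 6A likewise places the referral pathways inside the app.

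Follow-ups take place at t1, t2 and t3. The Figure 8 legend puts these at 4, 16 and 24 weeks after baseline. They are not confined to study participants. Adults who miss the inclusion criteria on age, origin, refugee background or problematic use may still use the app as Group 2, and Study Adherence says that "Group 2 will participate in a tombola with a minimum one in ten chance of winning a €15 gift after completing the measurements" at the same three time points.

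**The concern.** The lock exists to secure follow-up data. Help exists for a user who needs assistance now. If the first rule is applied literally, it overrides the second at each follow-up: someone who opens the app to find the crisis number meets a questionnaire first.

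This matters more here than in a supervised trial. The app is used stand-alone, and the Limitations section notes that there is no personal contact. The plan also expects some users whose AUDIT or CUDIT-R scores suggest dependence, and it warns heavy drinkers of the physical danger of stopping without professional help. At stake is prompt access to help for a vulnerable user. The trial's estimates are not involved.

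**Working it through.** No formula applies and the plan gives no figure to reproduce. The check sets the relevant statements side by side.

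1. **Scope of the lock.** It is stated in two places, both times for the app. A search of the article for an exempted module finds none.
2. **Location of the hotline.** It is described once, in the Help module (Referral Pathways, Table 1, Figure 6A legend). Help is part of the app, so it falls under the lock as worded.
3. **Another in-app route.** The personalized feedback encourages high scorers to seek help and names an example counseling center. It is given at the start, after baseline, and no hotline is mentioned there. It is not described as something that opens during a later lock.
4. **A sentence that might count as an exemption.** The section on structure lets participants use activated content as they need during the 4-week intervention phase. That covers the period before t1. The lock is stated in the very next sentence, without exception.
5. **When the lock can engage.** At three scheduled points: weeks 4, 16 and 24. No follow-up is pending before week 4.
6. **What stands in front of Help.** Table 2 marks five elements for follow-up: 30-day prevalence, confidence in change, PHQ-9, GAD-7 and the Program Participation Questionnaire. Two of these have item counts in the text: PHQ-9 with 9 and GAD-7 with 7, so 9 + 7 = 16 items before the other three are added. The article does not say whether a questionnaire can be skipped, dismissed or expires, so the actual delay cannot be established.
7. **Who falls under the rule.** The wording is not limited to Group 1, and Group 2 is measured at the same time points. A head count is not possible. Sample Size gives 450 to be assessed and at least 150 to be allocated, but these are trial recruitment targets. Group 2 is there to spread the app, which is a free download for anyone residing in Germany, and nothing caps it at 450 − 150 = 300. The 150 is not firm either: Sample Size treats it as a minimum and Participants as a maximum.

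**The case against.** The strongest objection is that a journal article is not a software specification. Neither lock sentence mentions Help, and Referral Pathways does not mention the lock. Which screens stay open behind a pending questionnaire is a detail that an article may leave to a fuller document. The evidence that could settle it is also missing: the legend "Implementation of the follow-measurements in the app" lists an entry screen (Figure 7A), and Figure 6A is the referral overview, but neither is shown. This stands as a limit on what can be said about the built app. It does not remove the point, because the article is not silent here. It states a rule twice, and following that rule has a poor consequence.

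A second objection is that the barrier is soft, and this is right. A measurement is pending only until it is completed, so the user can lift the lock. Help is open throughout the 4-week intervention and the number can be noted then. High scorers are referred to a counseling center at baseline, and the trained keypersons work in counseling and psychosocial centers. These routes reduce the consequence but do not replace the hotline. The Background itself counts shame and having to ask for help in person among the barriers that digital tools should bypass.

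Three stronger readings are tempting, and the document supports none of them. A reader might infer that users are cut off from the hotline, but the text implies only a delay that ends on completion. A reader might infer that the app did block Help in practice, but no screen is available to show it. A reader might infer that 150 to 450 users are affected, but that range has no sound bound at either end, and it would count users under the rule, not users harmed.

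**Conclusion.** The point holds as a defect in a stated rule. As written, a user with a pending t1, t2 or t3 assessment has to complete it before reaching the only crisis hotline the article describes. The barrier is temporary and can arise at three scheduled points. Its duration is unknown, and the number of users who would need help while a questionnaire is pending cannot be estimated.

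The conclusion assumes that the app follows the published wording and that a questionnaire cannot be bypassed. If the built app already leaves Help open, the defect is confined to the text. Completion rates, the mixed models and the sample size are untouched. The change is worth making because it improves participant safety at almost no cost.

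**What to change.** Limit the lock to the intervention modules in both sections that state it, for example: *Pending follow-up measurements will block further use of the intervention modules; the Help module, with the crisis hotline and counseling-center information, stays reachable for all users.* Put a Help link on the assessment entry screen if none is there.

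The cost is a change of wording in two places and, if the app follows the present text, a small software change. The downside is slightly less leverage for questionnaire completion, since one module stays open. The lock on the other modules, the push reminders, the gift cards for Group 1 and the tombola for Group 2 all remain. If the app already keeps Help open, only the wording needs correcting.
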